## Abstract

The study protocol of a prospective and randomized controlled trial for the assessment of the efficacy of nature activity therapy for people with Fibromyalgia (NAT-FM) is described. The primary outcome is the mean change from baseline in the Revised Fibromyalgia Impact Questionnaire (FIQR) score at post-treatment (12 weeks) and at 9 months of follow-up, and secondary outcomes are changes in the positive affect, negative affect, pain, fatigue, self-efficacy, catastrophising, and emotional regulation. A total of 160 patients with fibromyalgia will be divided into two arms: treatment-as-usual (TAU) and NAT-FM+TAU. Pre, during, post, +6, and +9 months assessments will be carried out, as well as an ecological momentary assessment (EMA) of intrasession and intersessions. Results will be subjected to a mixed group (NAT-FM+TAU vs. TAU) × phase (pre, post, +6 months, +9 months) general linear model. EMA intrasession measurements will be subjected to a 2 (pre vs. post) × 5 (type of activity) mixed-effects ANOVA. EMA between-session measurements obtained from both arms of the study will be analysed on both a time-domain and frequency-domain basis. Effect sizes and number needed to treat (NNT) will be computed. A mediation/moderation analysis will be conducted.

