### 2.2. Participants

A total of 160 patients with FM will be recruited from the Central Sensitivity Syndromes Unit (CSSU) at the Vall d’Hebron University Hospital (Barcelona, Spain). The sample size was established using IBM SPSS SamplePower 3.0 (IBM, Chicago, IL, USA), considering the results of a meta-analysis of therapies in nature [21], which reported an average effect size of *g* = 0.50, regarding clinical variables. With the anticipation of a 20% dropout and setting alpha = 0.05 and power 1-b = 0.80, the estimated sample size is *n* = 80 participants per condition. The sample size in each of the arms and the treatment follow-up period were estimated in such a way that they will be sufficiently representative to capture important results.

Patients visited consecutively by the physical therapist of the CSSU from November to December 2020 who met the selection criteria will be recruited. The inclusion criteria will be: (a) adults ≥18 years old, (b) to meet the 2010–2011 ACR diagnostic criteria for FM [1,37,38], and (c) to be able to understand and agree to participate in the study. The exclusion criteria will be: (a) participating in concurrent or past RCTs (previous year) and (b) exhibiting comorbidity with severe mental disorders (e.g., psychosis) or neurodegenerative diseases (e.g., Alzheimer’s) that would limit the ability of the patient to participate in the RCT.

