### 2.6. Statistical Analysis

Data analyses will be conducted by means of the statistical program SPSS v25 and MPlus 7.0. Initially, descriptive statistics will be calculated for all measures of the study (general, clinical characteristics/screening, and primary/secondary/additional secondary outcomes). Subsequently, multivariate analyses will be conducted to define the effect size of the intervention at the different assessment periods: CSA (pre, during, post, and follow-up) and EMA (during). Continuous variables will be analysed using the Kolmogorov–Smirnov test to assess normal distribution and the Levene test for equal variances. First, we will use the Student’s t-test to examine the baseline between-group differences in sociodemographic and clinical characteristics. The primary between-group analysis to assess the effect of treatment will be conducted on an intention-to-treat (ITT) basis with the FIQR total score as a continuous variable and assuming data missing at random. This involves using 2 × 4 mixed-effects ANOVA with the group (TAU+NAT-FM vs. TAU) as the between-groups factor and phase (pre, post, follow-up+6, follow-up+9) as the within-subjects factor. Corrected *ηp*^2^ (partial eta-square) will be estimated for the full model (group and phase main effects and group x phase interaction). We will also report the effect size (Cohen’s *d*) for each pairwise comparison, using the pooled baseline SD to weight the differences in the pre-post means and to correct for the population estimate. Separate models will be estimated for each of the secondary outcomes using the same analytical strategy. 

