In addition, to assess the clinical significance of the improvement in the primary outcome (FIQR), we will classify participants into two categories (responders vs. non-responders to treatment), using the following criterion: ≥20% reduction in the pre–post FIQR total scores [60]. This classification will be used to compute the number needed to treat (NNT) in NAT-FM compared with TAU. Finally, we will examine whether the effect of NAT-FM on the primary outcome at post and at the 6 and 9-month follow-ups is mediated/moderated through pre–post changes in secondary measures and personal factor variables (age, years from diagnosis, severity), using a structural equation model. According to the proposal of Luciano et al. [60], change scores before and after NAT-FM treatment will be calculated for these variables, as well as change scores before follow-up for the outcome variables. The analysis of temporality will increase the possibility of drawing conclusions about causality relationships. In this process, the data of the patients of the treatment with the greatest participation in the intervention will be analysed, defining participation as a minimum of 75% attendance of the sessions (per protocol analysis). The Benjamini–Hochberg correction for multiple comparisons will be applied; a procedure to detect false findings designed to overcome the limitations of other common procedures [61].

Complementary analyses will be conducted. Firstly, EMA intrasession measurements obtained from the NAT-FM treatment group will be subjected to a 2 (pre vs. post) × 6 (type of activity) mixed-effects ANOVA for pain, fatigue, self-efficacy, stress, and affect in order to assess the short-term impact of the planned activities. Secondly, EMA between-session measurements obtained from both arms of the study will be analysed both on a time-domain (single regression linear model for each dependent variable) and a frequency-domain basis (spectral analysis for each dependent variable) in order to assess transfer of the treatment effects to daily life.

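### The primary outcome is FIQR change at 12 weeks and 9 months, but the primary analysis is an omnibus group-by-phase ANOVA that tests neither time point and leaves the alpha and power of the claim unfixed

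*Protocol article*

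**What the plan says.** The Abstract ties the primary outcome, mean change from baseline in the Revised Fibromyalgia Impact Questionnaire, to two times ("FIQR) score at post-treatment (12 weeks) and at 9 months of follow-up"). It does not say whether both must succeed or either suffices.

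Section 2.6 describes the primary between-group analysis, by intention to treat, as a "2 × 4 mixed-effects ANOVA with the group (TAU+NAT-FM vs. TAU) as the between-groups factor" and "phase (pre, post, follow-up+6, follow-up+9) as the within-subjects factor". The 6-month visit is therefore in the model although the Abstract does not list it as a primary time. Partial eta-square is to be estimated for "group and phase main effects and group x phase interaction", and none of these terms is called decisive. The section adds: "We will also report the effect size (Cohen’s *d*) for each pairwise comparison". This promises effect sizes but designates no confirmatory contrast. Later, the mediation paragraph of the same section refers to the primary outcome at post, 6 and 9 months, so the set of time points also shifts.

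On multiplicity, section 2.6 says: "The Benjamini–Hochberg correction for multiple comparisons will be applied". The sentence follows the mediation and per-protocol text and names no family of tests.

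Section 2.2 derives 80 participants per condition from an average effect size of g = 0.50: "With the anticipation of a 20% dropout and setting alpha = 0.05 and power 1-b = 0.80". It gives no time point, number of measurements or within-patient correlation.

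**The concern.** The outcome asks two specific questions: is there a group difference in change at 12 weeks, and is there one at 9 months? The stated test asks a different one: do the group profiles differ in shape anywhere across four visits? A significant answer to the second does not establish either part of the first. Because no term or contrast is named as decisive, the deciding result could be picked after the data are seen. The sample size also has to belong to some test, and it is not the omnibus one. At stake are the meaning of the trial's confirmatory claim, its type I error and its power.

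**Working it through.** **Inputs.** From section 2.2: g = 0.50, alpha 0.05, power 0.80, dropout 20%, 80 per arm. From section 2.6: four phases, two groups. From section 2.5.1: FIQR test-retest r = 0.84, the only correlation given. Assumed: within-patient correlation ρ from 0.3 to 0.84, compound symmetry, effects in units of the FIQR SD.

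**1. The plan's own figure.** A two-sided two-sample t-test at 0.05 with d = 0.50 needs 63.8, so 64, per arm for 80% power. Then 64/(1 − 0.20) = 80. This matches. A one-sided test gives 50 per arm, or 63 after dropout, which does not match. The 80 is thus the size for one two-group comparison, without repeated measures and without a split of alpha.

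**2. What the interaction responds to.** With n = 64 per arm, the noncentrality is λ = (n/2) × Σ(δₜ − δ̄)²/(1 − ρ), with 3 and 378 df.

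- Sustained effect, δ = (0, 0.5, 0.5, 0.5): mean 0.375, sum of squares 0.375² + 3 × 0.125² = 0.1875.
- 6 months only, δ = (0, 0, 0.5, 0): mean 0.125, sum of squares 0.375² + 3 × 0.125² = 0.1875.

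The two sums are equal, so λ = 32 × 0.1875/(1 − ρ) = 6/(1 − ρ) in both cases.

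| ρ | λ | Power, sustained | Power, 6 months only |
|---|---|---|---|
| 0.3 | 8.6 | 0.68 | 0.68 |
| 0.5 | 12.0 | 0.84 | 0.84 |
| 0.7 | 20.0 | 0.97 | 0.97 |
| 0.84 | 37.5 | >0.99 | >0.99 |

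**3. Alpha for a two-time-point claim.** Under compound symmetry, two change scores sharing a baseline correlate 0.5 whatever ρ is.

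- Either time suffices, each at 0.05, uncorrected: 1 − P(|Z₁| < 1.96, |Z₂| < 1.96) = 9.1%.
- Both required, each at 0.05: no split of alpha is needed.
- Benjamini–Hochberg on exactly these two tests: 4.8% at correlation 0.5, and 4.3% to 5.0% over correlations 0.84 to 0.
- Interaction as a gate, then either time at 0.05: about 3% if nothing differs anywhere, but 8% to 9% if only 6 months differs by 0.5 SD.

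**4. Power if both times are required.** The variance of a change score is 2(1 − ρ), so the mean of each test statistic is 0.5/√(2 × 2(1 − ρ)/64). The two tests correlate 0.5.

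| ρ | Power at each time | Power for both |
|---|---|---|
| 0.5 | 0.81 | 0.70 |
| 0.7 | 0.95 | 0.92 |
| 0.84 | >0.99 | >0.99 |

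**5. Baseline adjustment.** The residual variance is 1 − ρ² after adjustment and 2(1 − ρ) for change scores, a ratio of (1 + ρ)/2. At ρ = 0.5, 0.7 and 0.84 the ratio is 0.75, 0.85 and 0.92, a reduction of 25%, 15% and 8%.

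**The case against.** In a design with a baseline visit, the group-by-phase interaction is the natural treatment test. It holds 5% for its own null, and for a sustained 0.5 SD effect it has at least 84% power once ρ reaches 0.5. Benefit confined to 6 months is an unusual pattern, and the promised pairwise effect sizes would expose it. An article also commonly leaves testing order and correction family to an analysis plan. Much of this stands, and it limits the point in four ways.

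- A reader might infer that the 5% level does not apply at all or is shown to be exceeded. It is not: the outcome depends on a success rule and a correction family that the article does not state.
- A reader might infer that Benjamini–Hochberg cannot protect a primary claim. On these two positively correlated tests alone it would hold about 5%; the gap is the undefined family.
- A reader might infer that the trial is underpowered. Step 4 shows power for both times below 80% at ρ = 0.5 and well above it at 0.7.
- A reader might criticise the group main effect for averaging in baseline. Section 2.6 does not make that term decisive, so nothing rests on it here.

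What the objection does not remove is the mismatch itself. The article states both the primary outcome and the primary analysis, and they address different questions. Descriptive effect sizes after an omnibus test do not make a confirmatory contrast.

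**Conclusion.** The point holds as a mismatch between stated outcome and stated test. A significant interaction is equally likely (0.68 to above 0.99 over ρ from 0.3 to 0.84) whether a 0.5 SD benefit is present at all three later visits or only at the one that is not a primary time. The stated 80% power belongs to a single two-group comparison; actual power for the interaction or for a two-time claim may be lower or higher. Alpha for the primary claim is undetermined: about 9% for an uncorrected either-wins rule, and 5% or less under a both-required rule or Benjamini–Hochberg on just the two tests.

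These figures assume compound symmetry, 64 completers per arm and the stated range of correlations. The document gives no correlation at the trial's own intervals. The equality of the two interaction powers does not depend on the value of ρ. Entering baseline as a repeated level is valid; adjusting for it as a covariate is an efficiency gain, not the correction of an error.

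**What to change.** In section 2.6, define the primary test as the NAT-FM+TAU minus TAU difference in FIQR at 12 weeks, adjusted for baseline FIQR and taken from the longitudinal model, at two-sided 0.05. Test the 9-month difference at 0.05 only if the 12-week test is significant; this fixed sequence needs no split of alpha. Report the 6-month difference and the omnibus F-tests as supportive. Apply Benjamini–Hochberg to the secondary outcomes and say so. In section 2.2, state that the 80% power refers to the 12-week contrast; the 80 per arm then stands unchanged. Align the Abstract with this order.

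The change is to wording and analysis only, with data already planned. Its cost is that 9 months cannot be claimed if week 12 fails. If the investigators want both times on an equal footing, they should state the both or either rule with the matching alpha and sample size. For example, testing each time at 0.025 with d = 0.50 and 80% power per test needs 78 per arm, or 78/0.8 = 97.5, so 98, after dropout.

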## 1. Introduction

According to the American College of Rheumatology (ACR), Fibromyalgia (FM) is a chronic disease of unknown etiology, characterised by the presence of generalized musculoskeletal pain and other symptoms, such as fatigue, waking unrefreshed, and cognitive problems [1]. The etiopathogenesis of FM involves several mechanisms, the most notable of these being the sensitization of the central nervous system (CNS). Abnormalities in the ascending and descending pathways associated with pain processing have been observed in FM [2]. The chronic nature of pain, wide range of symptoms, and comorbidity with mental disorders (mainly anxiety and depression) strongly impact on the well-being and quality of life of patients with FM [1,3,4].

Currently, the prevalence of FM among the general population is estimated to be around 2% worldwide and 2.6% in Europe [5]. In Spain, a prevalence of 2.4% is reported in the general population over 20 years of age, corresponding to 4.2% for women and 0.2% for men [6]. The direct costs (medical care, prescription of medicines, etc.) and indirect costs (absenteeism from work, loss of work, etc.) of FM are close to 11 billion € per year [7]. Due to the variety of complex factors involved in FM, recent years have seen the development and testing of various pharmacological [8] and non-pharmacological [9,10] treatments for management of the condition. The side effects associated with pharmacological treatments, along with their suboptimal clinical effects, have recently prompted the European League against Rheumatism (EULAR) to recommend that these treatments should only be used to control pain and sleep disturbances caused by FM [11].

Multicomponent treatments integrating exercise therapy (ET), cognitive behavioural therapy (CBT), and pharmacological treatment have generally been one of the most beneficial alternatives for improving quality of life, increasing functional capacity, and decreasing chronic pain in FM patients [12]. Randomized controlled trials (RCTs), testing for the simultaneous combination of ET and CBT, have been shown to be the most effective non-pharmacological treatments for FM [13]. Treatments based exclusively on ET have contributed to the reduction of symptoms of pain, fatigue, and depression, as well as to the improvement of mental health, psychological well-being, and physical function [14,15]. CBT-based treatments have favoured the acceptance of FM, strengthening of self-efficacy, development of coping strategies, and the reduction in depressive moods [16]. Pain neuroscience education (PNE) has been shown to be more effective than biomedical education [17] for FM and it is proving to be a key strategic piece in both the physical and cognitive approach of FM patients [18,19,20].

The strengths of such treatments, coupled with the identified benefits of exposure to natural contexts for people’s mental health, justify the need to explore new interventions for FM patients conducted in nature. Considering the moderate benefits that have been reported for the four therapeutic components mentioned above, it seems necessary to test empirically, for the first time, the synergistic effects of its combination. There is some evidence that nature can exert a synergistic effect when added to other therapeutic ingredients [21,22,23,24,25,26]. In this context, the Nature, Activity Therapy for people with Fibromyalgia (NAT-FM) project has emerged as a new generation of therapeutic treatments for intervention of health problems, which integrates CBT, PNE [27], ET, and nature exposure. Although activity-based interventions in nature have demonstrated positive effects for treating emotional, cognitive, and behavioural functioning in both the general population [28,29,30] and clinical population [31,32], as far as we know there is only one clinical trial that provides empirical evidence of their efficacy in FM patients [33]. 

This paper describes the design characteristics of the NAT-FM treatment in comparison with a treatment-as-usual (TAU). The objectives of the RCT are the following: (a) to analyse the efficacy of the NAT-FM program as an add-on to TAU in improving the functional status (primary outcome) of FM patients; (b) to compare the efficacy of NAT-FM treatment with respect to TAU in improving affectivity, emotional regulation, perceived competence, self-esteem, self-efficacy, anxiety, depression, and other secondary outcomes; and (c) to identify factors that may act as mediators or moderators of the efficacy of NAT-FM treatment (age, years of evolution, psychological inflexibility, etc.). 

## 2. Materials and Methods 

### 2.1. Research Design

The RCT protocol was developed following the Standard Protocol Items: Recommendations for Interventional Trials (SPIRIT) [34] and has been registered with ClinicalTrials.gov (Trial registration: NCT04190771). This study will employ a 9-month, randomized controlled trial (RCT) design, with two treatment arms. For the reporting of the RCT, we will follow the guidelines of the Consolidated Standards of Reporting Trials (CONSORT) [35]. The two arms of the treatment will be: (a) TAU (control group) and (b) TAU+NAT-FM (intervention group). Patients in both arms received TAU, since NAT-FM will, in principle, be a complementary treatment to that which is usually provided by the Spanish National Health System [36].

### 2.2. Participants

A total of 160 patients with FM will be recruited from the Central Sensitivity Syndromes Unit (CSSU) at the Vall d’Hebron University Hospital (Barcelona, Spain). The sample size was established using IBM SPSS SamplePower 3.0 (IBM, Chicago, IL, USA), considering the results of a meta-analysis of therapies in nature [21], which reported an average effect size of *g* = 0.50, regarding clinical variables. With the anticipation of a 20% dropout and setting alpha = 0.05 and power 1-b = 0.80, the estimated sample size is *n* = 80 participants per condition. The sample size in each of the arms and the treatment follow-up period were estimated in such a way that they will be sufficiently representative to capture important results.

Patients visited consecutively by the physical therapist of the CSSU from November to December 2020 who met the selection criteria will be recruited. The inclusion criteria will be: (a) adults ≥18 years old, (b) to meet the 2010–2011 ACR diagnostic criteria for FM [1,37,38], and (c) to be able to understand and agree to participate in the study. The exclusion criteria will be: (a) participating in concurrent or past RCTs (previous year) and (b) exhibiting comorbidity with severe mental disorders (e.g., psychosis) or neurodegenerative diseases (e.g., Alzheimer’s) that would limit the ability of the patient to participate in the RCT.

### 2.3. Procedure

The main researcher ([name]) will, through an initial interview, provide an overview of the study to FM patients interested in participating who met inclusion and exclusion criteria. Prior to being randomly allocated to treatments (TAU or TAU+NAT-FM), informed consent forms will be collected, which will include a detailed description of the characteristics of the interventions. Patients will also be informed that their participation will be voluntary and that they will be able to withdraw at any time, with the guarantee that they will continue to receive their usual treatment. This research will be conducted in accordance with the ethical standards set forth in the 1964 Declaration of Helsinki and was approved by the hospital’s Ethics Committee (PR(AG)120/2018). Patient data will be treated confidentially, ensuring that only the research team can access this information after recoding the name and personal identity number. Only the principal investigator will have access to the patient code key, which, according to current data protection legislation in Spain, will be stored separately in a safe place. The participants will be assigned to the intervention group (TAU+NAT-FM) or control group (TAU), employing a SPSS v25 randomization list.

The pharmacological treatment will not be modified during the RCT. Only rescue paracetamol (maximum 1 gram every 8 hours) will be allowed if there is worsening of pain. Patients will be evaluated before (pre), after the 6th session of treatment (during), and after (post) treatment, as well as 6 and 9 months after baseline assessment (follow-up). Measurements shall be made according to the time established for their administration: (a) Classical structural assessment (CSA): pre, during, post, and follow-up; and (b) ecological momentary assessment (EMA): intrasession (session log) and intersessions (day log between sessions). The flow chart of the RCT is presented in Figure 1. 

#### Forecast Execution Dates

Recruitment of patients: November 2019Finalisation of patient monitoring period: July 2020Publication of results: June 2021

### 2.4. Treatments

#### 2.4.1. Intervention Group (TAU + NAT-FM)

NAT treatments are a new generation of therapeutic programs for health intervention, in which CBT, PNE [27], ET, and nature exposure are integrated. NAT-FM is conceived as an add-on therapy and, in particular, has the primary therapeutic objective of helping patients to improve their functional status. The secondary objectives are to contribute to improving their affectivity, emotional regulation, and self-efficacy, as well as to reduce their perception of pain, fatigue, and catastrophising. Other variables that are usually improved by these treatments are perceived competence, self-esteem, stress, sleep quality, anxiety, depression, psychological inflexibility, kinesiophobia, physical function, and functionality. Table 1 and Table 2 show an outline of the NAT-FM.

The NAT-FM design process was guided by the procedures established in the protocol and the proof of concept study. The therapeutic objectives were selected by taking into account the results of a systematic review of the psychological characteristics of people with FM (affective, cognitive, metacognitive, and personality profiles) [39] and the validation of a panel of experts made up of researchers and psychologists ([name], [name], [name], [name], [name], and [name]), who evaluated the existing scientific evidence and the clinical and investigative relevance of each objective. The panel concluded that the processes to be included in the treatment are self-efficacy, negative affect, positive affect, emotional regulation, and catastrophising. The activities indicated in Table 1 were selected considering the results of an empirical study on the therapeutic potential of 10 activities in nature [40]. The number of activities practiced in each session was adapted according to the established targets, taking into account the progression of the patients and the evolution of the treatment. The activities addressing each target were selected considering the therapeutic potential identified by the expert panel.

The sectors (natural spaces) in which the outdoor sessions will be conducted have been validated by experts to guarantee their suitability for the treatment activities [40]. The geographical areas are Sant Genís Forest (coordinates N 41° 25.930 E 2° 8.237) and Les Escletxes del Papiol (coordinates N 41° 26.319 E 2° 1.101). The researchers conducted a proof of concept study ([name], [name], [name], and [name]) in these sectors to test the manualisation of procedures and to evaluate the suitability of the NAT-FM structure based on the testing of a series of representative sessions [41]. 

The protocol of the NAT-FM is the result of the consensus of the proposed instruments, of the moments of assessments corresponding to each phase of the treatment, and of the administration platforms used. The decision to combine different assessments (CSA+EMA) is motivated by the need for a strategy that could obtain more precise information about the dynamics of the variables to be evaluated and, in particular, could record the affective and cognitive impact of each activity, as well as its transfer to everyday life. The frequency of administration of the EMA has been established from analysing the results of a systematic review on the characteristics of its use in studies with patients with chronic pain [42]. 

The NAT-FM treatment will be carried out in a group-based format in groups made up of a maximum of 20 patients per session with a total of 12 weekly 2 h sessions (1 session per week). The sessions will be directed by the [name], who is a physiotherapist of the CSSU of Vall d’Hebron University Hospital and also a psychologist and sports technician with the required legal qualifications for conducting this activity.

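### NAT-FM is delivered in shared therapy groups, but the sample size and the primary model treat all patients as independent; if outcomes correlate within groups, the planned test is too liberal

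*Protocol article*

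**What the plan says.** Section 2.4.1 (Intervention Group) gives NAT-FM in a "group-based format in groups made up of a maximum of 20 patients per session", with 12 weekly two-hour sessions directed by one leader. Section 2.4.2 (Control Group) describes TAU as medication fitted to each patient plus advice, with no therapy groups.

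Section 2.2 (Participants) takes its effect size from a meta-analysis that "reported an average effect size of *g* = 0.50". "With the anticipation of a 20% dropout and setting alpha = 0.05 and power 1-b = 0.80", it concludes that "the estimated sample size is *n* = 80 participants per condition". It mentions neither an ICC nor a design effect.

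Section 2.6 (Statistical Analysis) names the primary analysis as a 2 × 4 "mixed-effects ANOVA with the group (TAU+NAT-FM vs. TAU) as the between-groups factor" and phase (pre, post, +6 and +9 months) as the within-subjects factor. The secondary outcomes follow the same strategy. Therapy group appears in neither the sample size nor the model.

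**The concern.** Patients in one NAT-FM group share sessions, peers and calendar dates for 12 weeks, and TAU patients share nothing comparable. The design is therefore partially nested, with clustering in one arm only. If outcomes are positively correlated within therapy groups, an analysis with only arm and phase understates the variance of the NAT-FM mean.

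The error favours the intervention: p-values on the primary FIQR comparison come out too small and confidence intervals too narrow. It carries over to every secondary outcome. The Benjamini–Hochberg correction in section 2.6 cannot repair p-values that are already too small. If therapy-group membership is not recorded, the analysis cannot be corrected later.

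**Working it through.** **Inputs from the protocol.** Alpha 0.05, power 0.80, dropout 20%, g = 0.50 and 80 per arm (section 2.2); at most 20 patients per therapy group (section 2.4.1); individual care in TAU (section 2.4.2); arm and phase as the only model factors (section 2.6).

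**Assumptions.** ICC 0.01, 0.05 or 0.10, because none is given; total variance 1 in each arm; equal group sizes; 64 completers per arm.

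**1. Reproduce the stated n.** A two-sided, two-sample t-test at d = 0.50 needs 63.8, so 64 per arm (power 0.801). Then 64/(1 − 0.20) = 80, which matches. A one-sided test would give 50, then 63 per arm, which does not. The 80 is therefore an independent-patients figure with no allowance for clustering.

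**2. Number of groups.** 80/20 = 4 is the minimum; after 20% dropout that leaves 4 groups of 16. Because 20 is a maximum, 8 groups of 10 (8 of 8 after dropout) are used as a second case.

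**3. Variance of the arm difference** at one time point, with k groups of m completers:

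V = ICC/k + (1 − ICC)/64 + 1/64 = (1 + DEFF)/64, where DEFF = 1 + (m − 1) × ICC.

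The unadjusted test assumes 2/64, so the inflation is R = (1 + DEFF)/2.

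- True type I error of the unadjusted test = 2[1 − Φ(1.96/√R)].
- z-based power of a test with the correct variance = Φ(0.5/√V − 1.96).

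Example with 4 groups of 16 and ICC 0.05:

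- DEFF = 1 + 15 × 0.05 = 1.75, V = 2.75/64 = 0.0430, R = 1.375.
- Type I error = 2[1 − Φ(1.96/1.173)] = 9.5%.
- Power = Φ(0.5/0.2073 − 1.96) = Φ(0.45) = 0.67.

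| Groups | ICC | R | Type I error | Power (z) | Power (Satterthwaite) |
|---|---|---|---|---|---|
| 4 of 16 | 0.01 | 1.08 | 5.9% | 0.78 | 0.69 |
| 4 of 16 | 0.05 | 1.38 | 9.5% | 0.67 | 0.55 |
| 4 of 16 | 0.10 | 1.75 | 13.8% | 0.57 | 0.43 |
| 8 of 8 | 0.01 | 1.04 | 5.4% | 0.79 | 0.76 |
| 8 of 8 | 0.05 | 1.18 | 7.1% | 0.74 | 0.70 |
| 8 of 8 | 0.10 | 1.35 | 9.2% | 0.68 | 0.63 |

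A simulation of the unadjusted t-test with 4 groups of 16 (40,000 runs) gave 5.7%, 9.5% and 14.0%, in agreement.

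**4. How much of the Satterthwaite loss is clustering?** The degrees of freedom are V²/[(1/64)²/63 + (DEFF/64)²/(k − 1)]. With k = 4 and ICC = 0 this is 4/(1/63 + 1/3) ≈ 11.5, and power is already 0.73. Part of the fall to 0.69 / 0.55 / 0.43 is thus the price of having few groups, not of correlation.

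**5. What the baseline score can do.** For a pre-post change with correlation r, V is multiplied by 2(1 − r). At r = 0.5 the factor is 1, so nothing is gained. At an assumed r = 0.7 it is 0.6. With 4 groups and ICC 0.05 on the change score, V = 0.6 × 0.0430 = 0.0258, and power is Φ(0.5/0.1606 − 1.96) = 0.88 (z) or 0.77 (Satterthwaite). R does not involve r, so for a given ICC on the change score the type I error stays at 9.5%.

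**The case against.** - **No ICC is given, so the size is assumed.** This stands. At ICC 0 the nominal 5% and 80% hold, and at 0.01 the departure is small. One leader directs all sessions, which removes between-therapist variation. It does not remove dependence from shared peers and sessions.
- **Four groups is the extreme case.** This stands, which is why 8 groups are shown. At ICC 0.05 the type I error is then still 7.1%.
- **Power may not fall below 80%.** A reader might infer that the plan certainly fails to deliver its power and alpha, or that 80% power survives only at an ICC of exactly zero. The documents do not support either. The planned model includes the pre phase, so power also depends on a pre-post correlation that is not stated. Section 2.5.1 gives an FIQR test-retest reliability of 0.84, but the correlation over 12 weeks could be lower. This answers the power part only. The standard error is still too small whenever the relevant ICC is positive.
- **The article condenses a fuller plan.** Random-effect structure and degrees of freedom are often left to an SAP, so the model half of the point is the softer one. However, section 2.6 defines the model by its factors, and no SAP can put clustering into the published derivation of 80 per arm.
- **The remedy does not restore power.** Correct. On the single-time-point z basis with 16 completers per group, restoring 80% would mean randomising about 85 / 109 / 138 per arm at ICC 0.01 / 0.05 / 0.10. From the formula, n = (1 + DEFF) × (2.80/0.5)², giving 68 / 87 / 110 completers, each divided by 0.80.

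**Conclusion.** The point holds in conditional form. NAT-FM is delivered in at least 4 shared groups and TAU is not, yet neither the sample size nor the stated model allows for this, and nothing else in the protocol corrects it. For any positive correlation within therapy groups, the primary test rejects too often. Over the assumed ICC range, type I error runs from 5.9% to 13.8% with 4 groups and from 5.4% to 9.2% with 8.

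The effect on power is less certain. On the basis that reproduces the stated n, z-based power is 0.57 to 0.78 (4 groups) or 0.68 to 0.79 (8 groups). A pre-post correlation well above 0.5 could make up the loss. These figures are for one time point. The arm-by-phase test is affected in the same direction when therapy groups differ in their change over time.

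**What to change.** 1. Record a therapy-group identifier for every NAT-FM patient.
2. Fit the primary and secondary models with a random therapy-group effect in the NAT-FM arm only, none in TAU, and small-sample (Satterthwaite) degrees of freedom. The effect should act on change from baseline, because a term constant over phases cancels out of the arm-by-phase contrast. State that the variance component will be imprecise with few groups.
3. Replace the single 80% power statement with power over stated ranges of ICC (such as 0.01 to 0.10), number of groups and baseline correlation.

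No extra patients or procedures are required. The cost is one more model term, wider intervals and a less favourable stated power. The change protects the type I error and makes any power shortfall visible, but does not remove it.
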